**Fig. 1 Fig1:**
[figure not shown]
Flowchart of patient selection and randomization

### Outcomes and measurements

#### Primary outcome

The primary outcome is the incidence of first all-cause unplanned readmission or mortality within 6 months post-randomization.

#### Secondary outcomes

Secondary outcomes will be measured at three, 6 and 12 months. Data will be collected by telephone at three and 12 months and at 6 months by a home visit of a blinded research nurse. Table 3 provides an overview of the data collection on different time points. The secondary outcomes are the following:The incidence of the first all-cause unplanned hospital readmission or mortality within 3 months and 12 months after randomization (triangulated by self-reporting and hospital data management system)Activities of Daily Living (ADL)- / instrumental ADL-functioning at 3*,* 6 and 12 months after randomization (the AMC Linear Disability Score) [35]Functional capacity at 6 months after randomization (Short Physical Performance Battery [36] and 2-min step test [37])Medication adherence (questionnaire and pharmacy dispensing records) at 3*,* 6 and 12 months after andomizationAnxiety and depression at 6 months after randomization (HADS-anxiety [38] and Geriatric Depression Scale-15 [39])Health-related quality of life at 6 and 12 month after randomization (EuroQol-5D-5 L) [40]Healthcare utilization at 3*,* 6 and 12 months after randomization (extension of *The Older Persons and Informal Caregivers Survey - Minimum Data Set (TOPIC-MDS)* [41] including readmission, emergency visits, GP visits, physical therapy and cardiac rehabilitation)Caregiver burden, at 6 and 12 months after randomization (TOPIC-MDS) [41]

### Statistical analyses

All analyses will be performed according to a predefined statistical analysis plan, which is published in the Netherlands Trial Register (NTR6316). The primary analyses will be performed according to the intention-to-treat principle. Outcomes will be reported as unadjusted risk differences and their 95% confidence intervals. Adjusted analyses using multivariable logistic or linear regression models, as appropriate, will focus on the incidence proportion of the composite endpoint of readmission and mortality up to 6 months. All analyses will be adjusted for the following potential confounders: age, sex, Charlson Comorbidity Score, MMSE, cardiovascular diagnosis, length of stay and living arrangement. In addition, subgroup analyses will be performed for cardiac diagnosis, frailty status with the VMS screening tool, cognitive status with the MMSE and social economic status. Data will be collected by an electronic Case Record Form in Research Manager [25], a web-based data management program. Multiple imputation will be used as a sensitivity analysis to assess the impact of missing values.

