### Sample size calculation

The sample size calculation is based on findings in a relevant subpopulation (101/674) of cardiac patients of the Transitional Care Bridge program [17], a comparable study including hospitalized patients ≥ 65 years at high risk of functional decline. Based on a six-month incidence rate of 44% (readmission and mortality combined) in the usual care subpopulation of the Transitional Care Bridge program and a minimal important difference of 12.5% in absolute risk reduction (from 44 to 31.5%) in patients in the intervention arm, (2-sided alpha of 0.05; power of 80%), a sample size of 235 patients per group is required. To compensate for an assumed 5% loss to follow-up, the total sample size per group will be 250 (Fig. 1).

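### The statistical section is inconsistent on whether the primary 6-month comparison is adjusted, and the article names neither result as decisive

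*Protocol article*

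**What the plan says.** The protocol article defines one primary outcome: "The primary outcome is the incidence of first all-cause unplanned readmission or mortality within 6 months post-randomization". It is binary at 6 months.

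The Statistical analyses section makes four statements that bear on it, in this order:

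1. "The primary analyses will be performed according to the intention-to-treat principle". Nothing else is labelled primary: no estimator, no effect measure, and no choice between adjusted and unadjusted.
2. "Outcomes will be reported as unadjusted risk differences and their 95% confidence intervals".
3. "Adjusted analyses using multivariable logistic or linear regression models, as appropriate, will focus on the incidence proportion of the composite endpoint", up to 6 months. That endpoint is the primary outcome.
4. "All analyses will be adjusted for the following potential confounders: age, sex, Charlson Comorbidity Score, MMSE, cardiovascular diagnosis, length of stay and living arrangement".

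The Sample size calculation section sizes the trial on a "minimal important difference of 12.5% in absolute risk reduction", from 44% to 31.5%, with two-sided alpha 0.05 and 80% power. The Statistical analyses section also refers to a predefined statistical analysis plan in the trial register; that plan is not available to this review.

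**The concern.** Statement 2 says the reported effect is unadjusted. Statement 4 says every analysis is adjusted. Statement 3 directs the adjusted models at the same 6-month composite, so the two statements cannot be assigned to different endpoints.

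A trial with one primary outcome needs one comparison whose confidence interval gives the answer. If the unadjusted and adjusted results fell on different sides of 0.05, a reader holding only this article could not say which one was planned as decisive, and the choice could be made after the results were known.

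The two analyses also differ in more than precision. The covariate list includes length of stay. Randomization follows a baseline assessment made early in the admission, and the intervention starts in hospital. Length of stay is therefore generally unknown at randomization and could be affected by treatment. The list also omits study site, which is a stratification factor. The adjusted model as listed may thus not estimate the same effect as the unadjusted comparison.

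**Working it through.** **Step 1: which analysis does the stated sample size match?** Inputs from the Sample size calculation section: p1 = 0.44, p2 = 0.315, two-sided alpha 0.05 (z = 1.960), power 80% (z = 0.8416). With pooled variance and no continuity correction:

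n = [1.960·√(2·p̄·(1−p̄)) + 0.8416·√(p1(1−p1) + p2(1−p2))]² / (p1−p2)²

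- p̄ = 0.3775, so 2·p̄·(1−p̄) = 0.4700
- p1(1−p1) + p2(1−p2) = 0.2464 + 0.2158 = 0.4622
- n = (1.3437 + 0.5722)² / 0.015625 = 3.6704 / 0.015625 = 234.9, rounded up to **235 per arm**

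This matches the stated figure exactly. Allowing for 5% loss, 235 / 0.95 = 247.4, so 248; the stated 250 is consistent. The design calculation is therefore that of an unadjusted risk difference.

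**Step 2: would the scale change the size?** At the planning values the unadjusted odds ratio is (0.315/0.685) / (0.44/0.56) = 0.585. The log-odds-ratio formula gives (1.960 + 0.8416)² × (1/0.2464 + 1/0.2158) / (ln 0.585)² ≈ 238 per arm. The sample size is not materially affected.

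**Step 3: how often would the two analyses disagree?** Trials were simulated with 235 patients per arm and marginal risks held at 44% and 31.5%, using 1,500 runs per scenario. Each run had one normally distributed prognostic score. The unadjusted test was a Wald test of the risk difference; the adjusted test was the treatment coefficient in a logistic model with the score. The standard deviation (SD) of the score on the log-odds scale is an **assumption**, because the article gives nothing to fix it, so a range is shown.

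| SD of score (assumed) | Power, unadjusted | Power, adjusted | Trials with differing significance verdicts |
|---|---|---|---|
| 0.5 | 80.5% | 81.6% | 4.5% |
| 0.8 | 81.2% | 85.1% | 7.3% |
| 1.0 | 81.4% | 87.3% | 9.2% |
| 1.3 | 79.8% | 87.5% | 11.3% |

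The Monte Carlo standard error of a power near 80% is √(0.8 × 0.2 / 1500) ≈ 1 point, so the variation in the unadjusted column is noise.

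The direction of disagreement follows from the table. At SD 1.0 the two kinds of disagreement sum to 9.2 points and differ by 87.3 − 81.4 = 5.9 points. About (9.2 + 5.9)/2 ≈ 7.5% of trials are then significant only when adjusted, and about 1.7% only when unadjusted.

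**Limits.** The simulation uses one perfectly measured score instead of seven covariates plus site. It tests the logistic coefficient and not a standardized risk difference. It describes the planned effect, not the false-positive rate under no effect.

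**The case against.** The strongest reply is that there is no real conflict. An unadjusted estimate followed by an adjusted model is ordinary practice, and the section runs in that order. The sentence beginning with all analyses comes directly after the one on adjusted models and may simply list their covariates. Read as *all adjusted analyses*, the contradiction disappears. The sample size also points to the unadjusted risk difference, and the registered analysis plan may name the primary analysis.

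Much of this stands. The charitable reading is plausible and the design calculation favours it. But the text does not say so, and even on that reading neither result is called primary.

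A reader might also infer three stronger things that the article does not support:

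- **That the two methods are incompatible.** They are not; only the sentences conflict when read literally.
- **That the plan commits to an odds ratio that cannot be set against the 12.5-point difference.** The article never mentions an odds ratio. A logistic model can yield a standardized risk difference, and the unadjusted risk difference is directly comparable with 12.5 points. The gap between an odds ratio of 0.585 and a risk ratio of 0.315/0.44 = 0.716 would matter only if the former were reported and misread. Nor is the mention of linear models an error in itself, since a linear model on a binary outcome estimates a risk difference.
- **That the deciding effect is fixed nowhere.** This can be said of the article only, because the analysis plan is not at hand.

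Finally, one may say that preferring an adjusted primary analysis is a matter of choice. That is fair: naming the unadjusted risk difference as primary would also remove the inconsistency.

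**Conclusion.** The point holds as an inconsistency in the article's wording on the primary comparison, together with the absence of any label showing which result decides. It is worth correcting and does not threaten the design. The stated 235 per arm reproduces exactly and stays adequate under either choice.

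The practical size is modest. Significance verdicts would differ in roughly 4 to 11% of trials at the planned effect, mostly because the adjusted analysis has more power (about 82 to 87%, against about 80%). Those figures rest on assumed covariate strengths and on the planning risks being true. The inconsistency in the text does not depend on them. The conclusion is confined to this article; the registered analysis plan may already resolve it.

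**What to change.** Name one primary analysis on the scale used for sizing, and label the other supportive.

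- **Primary, preferred:** the 6-month risk difference with its 95% confidence interval, obtained by marginal standardization (g-computation) from a logistic model, with a delta-method or bootstrap interval. The model includes the stratification factors (study site, which the present list omits, and MMSE stratum) and only covariates known at randomization. Length of stay would leave the list on that rule.
- **Supportive:** the unadjusted risk difference with its 95% confidence interval.
- **Wording:** replace the opening of the covariate sentence with *All adjusted analyses will include*, followed by the revised list.

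This keeps the result directly comparable with the 12.5-point difference, respects the stratified randomization, gains some power from data already being collected, and removes a choice between results after the fact. If the sponsor prefers the unadjusted risk difference as primary, saying so and calling the adjusted result supportive also resolves the inconsistency.

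The cost is a few lines of text, slightly more analysis work, and a need for complete baseline covariates. The sample size stays at 235 evaluable and 250 randomized per arm. If the registered analysis plan already names the primary analysis, the article need only be brought into line with it.

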### Randomization and blinding

After patients are screened for eligibility and have provided informed consent to a cardiac research nurse (CRN), the baseline assessment will be performed. After the baseline assessment patients will be randomized to the intervention or control group. Stratified block randomization (1:1) will be used with pre-stratification by study site and cognitive status based on the MMSE (15–23 vs ≥ 24). To ensure allocation concealment, a web-based data management program (Research Manager, http://deresearchmanager.nl/nl/home/) [25] and random permuted blocks of variable sizes will be used.

Group assignment will be blinded to patients. They will be informed that the study aim is to study different forms of post-discharge care and will receive only general information about the study protocol according to the postponed informed consent procedure of Boter et al. [26] Patients will be blinded to the aim of the intervention to prevent a potential Hawthorne effect [27, 28]. At the end of follow-up, patients (or their caregivers) will be fully informed about the content of the study intervention and the allocated treatment they received. Healthcare practitioners who execute the intervention cannot be blinded. Outcome assessments will be performed by research nurses who are blinded to the allocated treatment. Statistical analyses will be performed according to a predefined statistical analysis plan (see Statistical Analysis paragraph) by investigators blinded to group assignment.

Due to the minimal expected side effects related to the intervention of the CCB care program a data monitoring committee is not mandatory for this trial.

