### Hospital care for all included patients

Table 2 shows the time frame and components of the CCB program in the intervention and control groups. All included patients will receive a CGA within 72 h after admission by a CRN, which will also serve as the baseline study measurement (Table 3). The CGA identifies health issues in the somatic, psychological, social and functional domains, including problems related to polypharmacy, malnutrition, fall risk, delirium, depression and quality of life. Cardiovascular risk factors (e.g. body mass index, smoking, alcohol use and physical performance) will also be assessed. Following assessment, consenting patients will be randomized to the intervention or control group.

**Table 2 Tab2:** Time frame and components of the Cardiac Care Bridge program and the control group

Time Frame	Intervention component	Baseline – outcome measures	Professionals involved	Intervention	Control
Clinical phase					
≤ 72 h after hospital admission	*CGA* ^a^	Baseline	CRN^b^	X	X
≤ 72 h after hospital admission	Integrated care plan		CRN^b^	X	
During hospital stay	Geriatric team consultation in case of ≥ 5 identified health issues or ≥ 1 psychological issue		CRN^b^, CNS^c^, geriatrician	X	
Discharge phase					
Before hospital discharge	In-person handover of the CGA^a^, integrated care plan and medical treatment plan		CRN^b^, CCRN^d^	X	
Before hospital discharge	Visit of CCRN^d^ to participant		CCRN^d^	X	
At discharge	Medical discharge letter		Cardiologist, GP^e^, CCRN^d^	X	X
Post-clinical phase					
≤ 2 days after hospital discharge	Home visit 1. Medication reconciliation and integrated care plan		CCRN^d^	X	
≤ 1 week	*Home visit 2. Intake home based cardiac rehabilitation and integrated care plan*		CCRN^d^, PT^f^	X	
Week 1	*Two home-based cardiac rehabilitation sessions*		PT^f^	X	
Week 2	*Two home-based cardiac rehabilitation sessions*		PT^f^	X	
Week 3	Home visit 3. lifestyle promotion and self-management		CCRN^d^ PT^f^	X X	
	*Two home-based cardiac rehabilitation sessions*		PT^f^	X	
Week 4	*Two home-based cardiac rehabilitation sessions*		PT^f^	X	
Week 5	*Two home-based cardiac rehabilitation sessions*				
Week 6	Home visit 4. Evaluation of integrated care plan and home-based cardiac rehabilitation		CCRN^d^ PT^f^	X X	
	*Two home-based cardiac rehabilitation sessions*				
≤ 12 weeks	Home visit 5. If indicated by the CCRN^b^				
3 months		Follow-up telephone	Research Nurse	X	X
6 months		Follow-up home visit	Research Nurse	X	X

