### Phase 1: Clinical phase

Patients randomized to the intervention group will receive an integrated care plan based on geriatric and cardiac conditions identified by the CGA. This plan will be developed by the CRN together with the patient as follows. The CRN discusses identified health issues, asks if the patient recognizes them and what issues they prioritize for treatment. The integrated care plan is used to prioritize care during the three phases of the intervention. In case of ≥ 1 health issue in the psychological domain or ≥ 5 potential health issues in total, the geriatrician will be consulted. If indicated, the CRN also consults with other disciplines.

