### Phase 2: Discharge phase

At least one day before discharge, the CCRN visits the patients to discuss and prepare discharge to home. A personalized face-to-face handover between the CRN and the CCRN is completed using a standardized discharge checklist. In case of logistical difficulties the handover is performed by video call via tablet. The CGA, integrated care plan and ongoing interventions are discussed. In addition, the current medical condition, medication prescriptions and therapy advices a patient needs to adhere to (e.g. fluid restrictions in case of heart failure) are discussed. Finally, the CRN contacts the primary care PT by telephone to arrange home-based cardiac rehabilitation.

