### Usual care

Patients in the control group will receive usual care during hospitalization and after discharge. During hospitalization, other disciplines are consulted as needed. The control group may receive geriatric care if the patients’ treating physician consults the geriatric team. All participating hospitals have a geriatric consultation team that can be consulted by the patients’ treating physician on indication. After discharge, care as usual may include medical care by a cardiologist according to the national cardiovascular guidelines and a cardiac nurse specialist, if available. Also, control group patients can be referred to center-based cardiac rehabilitation. According to the Dutch multidisciplinary guideline of cardiac rehabilitation, center-based cardiac rehabilitation consists two one-hour exercise sessions per week during 6 weeks [32]. However, it is expected that only a small number of patients in the control group will receive center-based cardiac rehabilitation due to their age, illness and clinical complexity.

Standard primary care will be provided in both the intervention and the control group. For non-cardiovascular problems, the GP is the primary healthcare provider. Optional care provision in the GP practice includes secondary prevention, medication titration, regular evaluations of physical health status and referral to other disciplines. In both groups the GP will be informed about the hospitalization by a discharge letter from the medical specialist. In the intervention group the GP is informed about the patients’ study participation by letter. During the intervention, the CCRN will be an extra liaison between care providers in case of medical, mental or social issues.

In the Netherlands virtually all citizens have basic healthcare insurance, which includes coverage of primary care visits, hospital outpatient visits, hospitalizations and prescribed medication. Dutch citizens can also purchase optional supplementary insurance, which includes physical therapy and other services.

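### Length of stay is fixed after randomization and can be changed by the intervention, so adjusting for it leaves every adjusted treatment effect open to bias

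*Protocol article*

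**What the plan says.** The covariate rule is in the protocol article, Statistical analyses: "All analyses will be adjusted for the following potential confounders: age, sex, Charlson Comorbidity Score, MMSE, cardiovascular diagnosis, length of stay and living arrangement". Nothing there limits length of stay to the days before randomization. The same section states that outcomes are reported as unadjusted risk differences with 95% confidence intervals, and that the adjusted regression models focus on the 6-month composite.

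The order of events is set out elsewhere in the article:

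- **Randomization and blinding:** "After the baseline assessment patients will be randomized to the intervention or control group". The baseline assessment is the geriatric assessment, due within 72 h of admission (Hospital care for all included patients, and Table 2). The Table 3 footnote says 48 h. Either way it is early in the stay.
- **Phase 1: Clinical phase**, on the first inpatient step given to one arm only: "Patients randomized to the intervention group will receive an integrated care plan based on geriatric and cardiac conditions identified by the CGA". With at least one psychological issue, "or ≥ 5 potential health issues in total, the geriatrician will be consulted".
- **Phase 2: Discharge phase**, on the last step before the patient leaves: "At least one day before discharge, the CCRN visits the patients to discuss and prepare discharge to home".
- **Usual care**, on what controls may get: "The control group may receive geriatric care if the patients’ treating physician consults the geriatric team".
- **Primary outcome**, on the event and its time origin: "The primary outcome is the incidence of first all-cause unplanned readmission or mortality within 6 months post-randomization".

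**The concern.** Randomization balances the arms on everything fixed before allocation. A variable fixed afterwards cannot confound assignment, and adjusting for one that treatment may alter gives up that protection. Length of stay raises three separate problems.

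1. **Mediation.** If the care plan, triggered consultation or pre-discharge nurse visit changes the stay, and the stay affects later readmission or death, adjustment removes that part of the effect.
2. **Collider path.** Sicker patients stay longer and have more events. If the intervention also moves the stay, intervention and control patients with the same stay differ in unmeasured severity. The model attributes that difference to treatment.
3. **Reverse dependence.** Follow-up runs from randomization and counts deaths. For a patient who dies before discharge, the primary event determines the covariate.

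The rule covers all analyses, so it reaches the adjusted primary result and the adjusted secondary outcomes.

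**Working it through.** **1. The plan's own figure.** Inputs from Sample size calculation: 44% against 31.5%, two-sided alpha 0.05, power 80%. With pooled variance and a mean risk of 0.3775:

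n = [1.960 × √(2 × 0.3775 × 0.6225) + 0.8416 × √(0.44 × 0.56 + 0.315 × 0.685)]² / 0.125² = (1.3437 + 0.5722)² / 0.015625 ≈ 235 per group.

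This matches the stated 235. Then 235 / 0.95 gives 248, which the plan rounds to 250. The calculation is for an unadjusted comparison of two proportions and does not depend on the covariate list.

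**2. Timing of each covariate.** Age, sex, Charlson score, MMSE, cardiovascular diagnosis and living arrangement are all collected at T0 in Table 3. Length of stay needs a discharge date. Table 3 records the hospitalization date at T0 but has no length-of-stay item. Between randomization and discharge, only the intervention arm has the care plan, the protocol-triggered geriatric consultation, and the nurse visit with handover.

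**3. Direction and approximate size.** The documents give no effect of the program on stay and no link between stay and outcome. The following values are therefore assumptions: stay L in SD units, correlation 0.5 with unmeasured severity U, U raising the event log-odds by 0.8 per SD, no effect of L itself, and a shift of δ SD in L in the intervention arm. Then E(U | L, T) = 0.5 × (L − δT). At equal stay the arms differ in severity by −0.5δ SD, so the approximate bias in the risk difference is −0.5δ × 0.8 × 0.44 × 0.56.

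- δ = +0.2: −0.08 × 0.2464 = −2.0 points.
- δ = +0.4: −0.16 × 0.2464 = −3.9 points.

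Simulation of 400,000 patients per scenario, with a logistic model standardized to a risk difference, gave these results in percentage points:

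| Shift in stay (SD) | No true effect: unadjusted | No true effect: stay-adjusted | True effect about −12: unadjusted | True effect about −12: stay-adjusted |
|---|---|---|---|---|
| −0.4 | +0.1 | +3.5 | −12.3 | −9.0 |
| −0.2 | +0.3 | +2.0 | −12.1 | −10.5 |
| 0 | −0.1 | −0.1 | −12.0 | −12.0 |
| +0.2 | −0.3 | −2.1 | −12.4 | −14.0 |
| +0.4 | −0.3 | −3.8 | −12.7 | −16.0 |

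**4. A second set of assumptions, in days.** No true effect; 44% risk; median stay 7 days; severity raising log-stay by 0.3 per SD and the event log-odds by 0.4 to 0.9 per SD; residual SD of log-stay 0.5. A log-stay shift of ±0.2 means 7 × (e^0.2 − 1) ≈ 1.6 days longer or 7 × (1 − e^−0.2) ≈ 1.3 days shorter. Stay entered as days or as log-days.

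- Shorter stay: adjusted risk difference +1.4 to +3.3 points.
- Longer stay: −1.6 to −2.9 points.
- No shift: the adjusted and unadjusted estimates agree.

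Other random draws move the ends of these ranges by about 0.2 points. Against the target effect, 1.4 / 12.5 = 11% and 3.3 / 12.5 = 26%.

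**5. Scale.** At 250 per arm, the standard error of the risk difference is √(0.44 × 0.56 / 250 + 0.315 × 0.685 / 250) ≈ 4.3 points, and the 95% half-width is about 8.4 points. In-hospital deaths were not simulated, because no rate is given.

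**The case against.** - **The unadjusted estimate is safe.** The section promises unadjusted risk differences and the sample size rests on them, so the adjusted model can be read as supportive. This stands, and it limits the damage. But the section also says all analyses are adjusted and does not say which estimate carries the conclusion.
- **An effect on stay is not shown.** The nurse visit is timed from discharge, the handover can take place by video call, and controls may also see the geriatric team. Discharge may therefore drive the intervention rather than the reverse. This also stands: the stay may be affected, and with no shift the severity path gives no bias. It does not justify a model that is valid only if the program leaves the stay unchanged.
- **The sizes are assumed and below one standard error.** Both are true. But bias does not average out, and here its direction depends on something the trial does not control.
- **In-hospital deaths may be few.** Patients with a life expectancy under 3 months are excluded, so this part may be small. Its size is unknown.
- **The registered SAP may define the term as days before randomization.** That would cure the problem. The SAP is not shown, and the article's wording does not say so.

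**Conclusion.** The concern holds. On the article's own sequence of events, length of stay is fixed after allocation, can be altered by inpatient steps given only to the intervention arm, and is cut short by deaths that count in the primary outcome. It is wrongly classed as a confounder, and every adjusted estimate is open to bias in either direction. The unadjusted intention-to-treat estimate and the sample size are unaffected.

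The size cannot be computed for this trial. It is nil if the program does not move the stay, leaving aside in-hospital deaths. Under the assumptions shown, it is about 1.4 to 3.3 points for a shift of about 20% and up to 3.8 points for a shift of 0.4 SD. How much this matters depends on whether the adjusted or the unadjusted estimate is primary, which the section leaves unclear.

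**What to change.** Delete length of stay from the covariate list and adjust only for variables fixed before randomization. If a proxy for severity at entry is wanted, use days from admission to randomization, or acute against elective admission. Report length of stay by arm as a descriptive process measure. In the same edit, state which estimate, unadjusted or adjusted, carries the primary conclusion.

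The cost is a wording change in the protocol, and in the registered SAP if it carries the same list. It needs no new data and leaves the sample size at 235 per group (250 after loss). It should be made before anyone sees results by arm.
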